## Abstract

**Introduction:**

Girls’ and women’s health as well as social and economic wellbeing are often negatively impacted by early childbearing. In many parts of Africa, adolescent girls who get pregnant often drop out of school, resulting in widening gender inequalities in schooling and economic participation. Few interventions have focused on education and economic empowerment of adolescent mothers in the region. We aim to conduct a pilot randomized controlled trial in Blantyre (Malawi) and Ouagadougou (Burkina Faso) to examine the acceptability and feasibility of three interventions in improving educational and health outcomes among adolescent mothers and to estimate the effect and cost-effectiveness of the three interventions in facilitating (re)entry into school or vocational training. We will also test the effect of the interventions on their sexual and reproductive health (SRH) and mental health.

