## Methods

### Study design

We will conduct a pilot RCT designed to estimate the effect of a conditional cash transfer and subsidized child care on adolescent mothers’ re-entry into school or vocation training. We also seek to examine the effects of the interventions on SRH outcomes and mental health as secondary outcomes, and to determine the most cost-effective interventions to increase adolescent mothers’ re-entry into school or vocational training. We will randomly assign adolescent mothers to one of three study arms. Adolescent mothers in all the arms will receive life skills training through adolescent mothers’ clubs. Adolescent mothers in arm two will also receive subsidized child care, while those in arm three will receive all three interventions. Comparing arm one (mothers’ clubs only) and arm two (mothers’ clubs + subsidized child care) will allow us to test the additional benefit of the subsidized child care. Comparing arms two and three (mothers’ clubs + subsidized child care + cash transfer) will also allow us to test the additional benefit of the cash transfer. Comparing arms one and three will allow us to test the combined benefit of the subsidized child care and cash transfers. The RCT design is summarized in Fig. 2.

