### Cost-effectiveness evaluation

The cost-effectiveness evaluations will examine the value for money of the three interventions in promoting adolescent mothers’ (re)entry and enrolment into school or vocational training, and document the additional value of the proposed interventions on SRH and mental health outcomes. The cost-effectiveness analysis will be carried out from the government-funded program perspective. The costing assessment will focus on the total costs that would be incurred by the government in delivering the integrated interventions. More specifically, we will assess the annual incremental costs of the delivery of each intervention including start-up and implementation costs.

The start-up costs will capture all the costs incurred for the preparation and introduction of the interventions while the implementation costs will consist of the costs incurred for the implementation of the intervention activities. These include incurred costs for the identification and hiring of program staff, identification of childcare centers to be involved in the intervention, development of the system for administering and monitoring the childcare voucher system, setting up of the cash transfer system, inception meetings including CHWs, initial training, cost associated with mentoring CHWs as they deliver the interventions, costs for sensitization and awareness-raising activities, supervision/monitoring during start-up as well as cost associated with overall coordinating activities and capital items acquired in the start-up. The start-up costs will be annualized accordingly.

The implementation costs will encompass all relevant costs such as the costs for mentoring and supervision, replenishment of capital items, mothers’ club operation costs, printing and materials, vouchers paid to childcare centers, amounts transferred in cash to adolescent mothers, and time invested by CHWs in facilitating the adolescent mothers’ clubs.

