### Data processing and analysis

Outcomes will be measured pre-randomization (at baseline) and at the end of the 12-month intervention period (endline). Quantitative data will be collected on Android-based tablets programmed using SurveyCTO. The data will be synchronized to a password protected server. The data will then be transferred to Stata for further cleaning and analyses.

At the endline, we will estimate the average treatment effect across the three groups using intent-to-treat (ITT) analysis, comparing school/vocational training enrolment at baseline and endline. Primary analyses will be unadjusted. We will also compute adjusted effects (controlling for covariates) to account for differential attrition or any differences at baseline. Drawing on financial records detailing the cost of the interventions (cash transfers, childcare vouchers, and cost of running the mothers’ clubs), we will conduct cost-effectiveness analyses of the interventions. The cost per (re)enrolled adolescent mother will be the primary measure of the cost-effectiveness of the interventions. This costing data per adolescent mother will be further combined with secondary effectiveness data to calculate additional cost-effectiveness estimates of the interventions. Secondary effectiveness data will be measured through improvements in mental health of adolescent mothers and improved knowledge and uptake of SRH practices.

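### The primary cost-effectiveness measure divides by all (re)enrolled mothers and names no comparator, so it does not give the cost per additional enrolment that objective 4 needs

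*Protocol article*

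**What the plan says.** Under Data processing and analysis, the article draws on financial records for cash transfers, childcare vouchers and the running of the clubs, and then fixes the measure: "The cost per (re)enrolled adolescent mother will be the primary measure of the cost-effectiveness of the interventions". No incremental ratio is defined there or elsewhere.

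Cost-effectiveness evaluation describes the costs in two ways. First, "The costing assessment will focus on the total costs that would be incurred by the government in delivering the integrated interventions". Then, as a closer specification, "we will assess the annual incremental costs of the delivery of each intervention including start-up and implementation costs".

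Study design gives clubs to everyone: "Adolescent mothers in all the arms will receive life skills training through adolescent mothers’ clubs". It sets up the between-arm comparisons. Arm two against arm one "will allow us to test the additional benefit of the subsidized child care", and arm three against arm two "will also allow us to test the additional benefit of the cash transfer". Arm three against arm one gives the two together. These contrasts are stated for benefit and are never linked to the cost measure.

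The Abstract promises "to estimate the effect and cost-effectiveness of the three interventions in facilitating (re)entry into school or vocational training". Objective 4, in the Background, concerns cost-effectiveness in raising re-entry. Primary outcome codes as a success any mother enrolled during the 12 months. Eligibility criteria and Exclusion criteria do not exclude mothers already in school or training.

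**The concern.** A funder wants to know what one further mother in school or training costs if childcare, or childcare and cash, is added. That is a difference in cost divided by a difference in enrolment. Dividing cost by everyone enrolled in an arm answers another question: what was spent per enrolled mother, whatever caused her to enrol.

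Two things enter the plain ratio that do not belong to the added component. The numerator, if it is the arm's total cost, carries the club cost common to all arms. The denominator carries background enrolment: mothers already enrolled at baseline and mothers who would have returned with clubs alone. The figure then depends on club cost and on the site's background schooling rate as well as on what the component achieves. Objective 4, and any advice on which component to fund, would rest on it.

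**Working it through.** The article gives no cost-effectiveness figure, so there is none to reproduce. The check compares the stated ratio with the incremental one.

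**Inputs from the article**
- Enrolled in the comparator arm: 94% out of school, hence 6% (Sample size and sample selection).
- Enrolled with intervention: 15 points better, hence 21% (same section).
- Cash: about US$30 per quarter, 4 × 30 = US$120 over 12 months (Conditional cash transfers).
- 90 mothers per arm (Sample size and sample selection).

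**Assumed, because the article gives no figure**
- Club cost C = US$50 to 200 and voucher cost V = US$60 to 120 per mother for the year.
- Cash paid for the full year, to enrolled mothers only.
- The 21% is placed in arm two, except where stated otherwise.

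**Step 1: background enrolment in the denominator.** 6 of the 21 points would be there without the added component: 6/21 = 29%. Study sites reports 82% out of school in Ouagadougou, so 18% in school. If the same 15-point effect applied there, the share would be 18/33 = 55%. Both surveys covered pregnant and parenting adolescents, which is not exactly the trial population.

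**Step 2: total cost over all enrolled (plain reading), arm two.** Ratio = (C + V)/0.21.
- V = 60: 110/0.21 = US$524 to 260/0.21 = US$1,238 as C runs from 50 to 200.
- V = 120: 170/0.21 = US$810 to 320/0.21 = US$1,524.

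**Step 3: incremental ratio, arm two v one.** [(C + V) − C]/(0.21 − 0.06) = V/0.15.
- V = 60: US$400. V = 120: US$800.
- Club cost cancels, so the result is the same for every C.

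**Step 4: incremental cost over all enrolled (the most favourable reading of the two cost passages).** Ratio = V/0.21.
- V = 60: US$286 against US$400. V = 120: US$571 against US$800.
- In both, 0.15/0.21 = 0.714, so the cost per additional enrolment is understated by 29%. This does not depend on V or C. At 33% against 18% it would be 15/33 = 0.455, an understatement of 55%.

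**Step 5: a component with no effect.** Let arms two and three both reach 21%, with C = 100 and V = 60.
- Arm two: 160/0.21 = US$762 per enrolled mother.
- Arm three: (160 + 120 × 0.21)/0.21 = 185.2/0.21 = US$882.
- The stated measure shows a US$120 gap. The incremental comparison shows US$25.20 more per mother for no extra enrolment, and the ratio is undefined.

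**Step 6: precision of the denominator at 90 per arm (simple binomial, no attrition or design effect).**
- 21% v 6%: SE = √(0.21×0.79/90 + 0.06×0.94/90) = 0.050; 95% interval about 5 to 25 points.
- 10% v 6% (an assumed smaller effect): SE = √(0.10×0.90/90 + 0.06×0.94/90) = 0.040; about −4 to +12 points.

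In the second case the interval spans zero, and an ordinary bootstrap interval for the ratio would not be interpretable.

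**The case against.** The strongest reply is that the article leaves the formula open and does not choose an average. The word average is not used for the cost measure, incremental costs are explicitly planned, and between-arm treatment effects are estimated in the same section. A condensed article may leave the exact ratio to a fuller document. This has some force: the cost wording is ambiguous. But the article does name its primary measure, and that measure has neither a comparator nor a count of enrolments gained. Incremental costs alone leave the 29% error of step 4. Reading (re)enrolled as excluding mothers already in school at baseline would not cure it either, since mothers who would have returned with clubs alone still count.

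A reader might infer more than the documents support:

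- *That the trial cannot show what childcare or cash buys.* It can. The component costs and the arm contrasts are all planned, and the increments can be derived from them.
- *That clubs in every arm are the obstacle.* They are not. Their cost and effect cancel in the between-arm differences. They rule out only a randomised figure for clubs against no intervention.
- *That the stated measure misstates a component several-fold or reverses a ranking.* No reversal has been shown. An arm's ratio falls below that of the preceding arm exactly when the increment costs less than the preceding arm's ratio, so the two usually point the same way. A several-fold gap appears when the whole arm three package is set against the cash increment alone, and those are different quantities.

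It is also fair to say that incremental ratios will be imprecise in a pilot. That bears on how they are reported and does not justify the other denominator.

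**Conclusion.** The point holds in this form: the stated primary measure, read plainly, counts background enrolment and is not tied to the arm contrasts, so it does not answer objective 4. The firm figure is a 29% understatement of the cost per additional enrolment when incremental cost is divided by all enrolled mothers. It rests only on the article's own 6% and 21%. The 55% for Ouagadougou also assumes that the 15-point effect carries over. The dollar figures are illustration, because club and voucher costs are assumed. The data collection is sound; what needs changing is the definition of the measure and the scope of the claim about three interventions.

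**What to change.** - Define the primary economic measure as the incremental cost per additional (re)enrolled mother: difference in mean cost divided by difference in the primary-outcome proportion, for arm two v one, three v two and three v one.
- Reconcile Cost-effectiveness evaluation with Data processing and analysis, so that it is clear which costs form the numerator and against which arm.
- Report the differences in cost and in enrolment with their joint uncertainty, by a cost-effectiveness plane, an acceptability curve, or net benefit over a range of willingness to pay. Do not rely on an interval for the ratio alone.
- Keep cost per enrolled mother as a descriptive figure for each arm.
- Limit the cost-effectiveness claim to childcare and cash added to clubs, and say that clubs against no intervention cannot be estimated in this design.

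The change costs some wording and a modest amount of analysis; no new data are needed. The price is imprecise ratios, as is to be expected in a pilot, and no cost-effectiveness figure for clubs alone.

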### Potential study limitations

While we will adopt a rigorous study design, there are several potential limitations of the study. First, although the selection of the interventions was informed by findings from surveys of pregnant and parenting adolescent girls in Burkina Faso and Malawi and dialogues with community members and other stakeholders, including adolescent mothers, these interventions may be perceived to have been selected in a top-down rather than participatory approach. Second, the one-year duration of the RCT may be too short to observe any effects particularly if there are restrictions on when adolescent mothers can (re)enroll in school or vocational training programs. Finally, there may be differential attrition by study arm between baseline and endline that may limit our ability to draw conclusive evidence on the effects of the interventions.

## Discussion

We expect that our research will generate rigorous evidence that can inform policies and programs aimed at promoting the wellbeing of pregnant and parenting adolescents. Our research builds on existing studies on the lived experiences of pregnant and parenting adolescents that were informed in part by inputs from various stakeholders in both countries. In addition, the interventions are informed by emerging evidence from these studies that underscore financial and childcare constraints as critical barriers to school re-entry for these adolescents. We therefore expect that our proposed interventions will respond to needs highlighted by pregnant and parenting adolescents themselves—majority of whom are out of school but express a desire to return to school and the wider community.

Community health workers play an important role in enhancing communities’ access to preventative health services including health promotion and education services [33]. In this study, we propose to work with CHWs to deliver life skills education to adolescent mothers through adolescent mothers’ clubs. Given their role as a bridge between the community and the health sector, CHWs may also facilitate adolescent mothers’ access to SRH, child health, and psychosocial services. This is particularly critical given the significant challenges that adolescent mothers face in accessing health services [34]. Through this project, we therefore expect to demonstrate the role that this cadre of health workers plays in enhancing adolescent mothers’ trust in the health system and, consequently, improving their health care seeking behavior.

## Data Availability

The research will generate anonymized, individual level qualitative and quantitative data capturing, among other indicators, sociodemographic characteristics, SRH, schooling and employment data from adolescent mothers. These data can be mined by other researchers seeking to answer a variety of public health and sociological questions relevant to adolescent and youth populations. Importantly, some of the data will be longitudinal and can be used to make causal inferences. De-identified data will be made publicly available for further analyses following a 2-year embargo after the finalization of the study.

## Abbreviations

AGI-K: Adolescent Girls Initiative-Kenya
CHW: Community health worker
EA: Enumeration area
IDI: In-depth interview
ITT: Intent-to-treat
PHQ-9: Patient Health Questionnaire-9
RCT: Randomized controlled trial
SRH: Sexual and reproductive health
SCTP: Social Cash Transfer Programme (Malawi)
STI: Sexually transmitted infection
UNIMAREC: University of Malawi Research Ethics Committee
